## Abstract

**Background:**

It has been estimated that between 5% and 10% of women diagnosed with breast cancer have a hereditary form of the disease, primarily caused by a *BRCA1 *or *BRCA2 *gene mutation. Such women have an increased risk of developing a new primary breast and/or ovarian tumor, and may therefore opt for preventive surgery (e.g., bilateral mastectomy, oophorectomy). It is common practice to offer high-risk patients genetic counseling and DNA testing after their primary treatment, with genetic test results being available within 4-6 months. However, some non-commercial laboratories can currently generate test results within 3 to 6 weeks, and thus make it possible to provide *rapid *genetic counseling and testing (RGCT) prior to primary treatment. The aim of this study is to determine the effect of RGCT on treatment decisions and on psychosocial health.

**Methods/Design:**

In this randomized controlled trial, 255 newly diagnosed breast cancer patients with at least a 10% risk of carrying a *BRCA *gene mutation are being recruited from 12 hospitals in the Netherlands. Participants are randomized in a 2:1 ratio to either a RGCT intervention group (the offer of RGCT directly following diagnosis with tests results available before surgical treatment) or to a usual care control group. The primary behavioral outcome is the uptake of direct bilateral mastectomy or delayed prophylactic contralateral mastectomy. Psychosocial outcomes include cancer risk perception, cancer-related worry and distress, health-related quality of life, decisional satisfaction and the perceived need for and use of additional decisional counseling and psychosocial support. Data are collected via medical chart audits and self-report questionnaires administered prior to randomization, and at 6 month and at 12 month follow-up.

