Newly diagnosed patients who learn that they are gene mutation carriers may decide to undergo a mastectomy rather than a lumpectomy, or bilateral mastectomy (BLM) rather than unilateral mastectomy. Recent studies have shown that BLM and delayed contralateral prophylactic mastectomy (CPM) substantially reduce the risk of contralateral breast cancer, while studies on survival have yielded mixed results [20-23]. Additionally, women who choose unilateral or bilateral mastectomy as their initial surgical treatment will often be spared the necessity of undergoing radiation therapy. However, rapid genetic counseling and testing (RGCT) may necessitate some delay in surgical treatment until DNA test results are available. Previous studies have indicated that the majority of newly diagnosed breast cancer patients at high risk of being *BRCA1/2 *mutation carriers will accept the invitation to undergo RGCT, and that the DNA test results can have a substantial impact on the choice of surgery [3,24,25]. In these British and American studies, between one-half and two-thirds of the breast cancer patients carrying a *BRCA1 *or *BRCA2 *mutation opted for a bilateral mastectomy, with some opting for a delayed CPM instead of direct BLM. Additionally, between 16% and 24% of high-risk patients who test negative for a *BRCA1/2 *mutation opted for BLM [3,25].

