### Objectives and research hypotheses

This study is evaluating the behavioral and psychosocial effects of the routine offer of RGCT to newly diagnosed primary breast cancer patients who meet criteria for being at-risk of having a *BRCA1 *or *BRCA2 *gene mutation. RGCT is being offered to women shortly after diagnosis, prior to surgery. The comparison group is composed of women who receive usual care (UC), in which RGCT is available but is rarely recommended or requested.

The specific research hypotheses are:

1. A significantly greater percentage of women in the RGCT group as compared to the UC group will undergo a direct bilateral mastectomy (BLM).

2. A significantly greater percentage of women in the RGCT group as compared to the UC group will undergo a delayed prophylactic contralateral mastectomy (CPM).

3. Women in the RGCT group will report significantly lower levels of perceived cancer risk, cancer worries, and cancer-related distress at 12 month follow-up than women in the UC group.

4. Women in the RGCT will have significantly higher levels of knowledge of genetic issues in breast cancer, and higher levels of decisional satisfaction than women in the UC group.

5. Following from hypotheses 1 and 2, women in the RGCT group will report significantly more problems with body image and sexuality than those in the UC group. No significant differences will be observed between the RGCT and the UC groups on other HRQL outcomes.

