## Methods/Design

This is a multicenter, randomized, controlled trial in which patients are randomized to RGCT or to UC on a 2:1 basis. The primary clinical outcomes include: the uptake of direct BLM or of delayed CPM. Data on surgical outcomes will be abstracted from the medical records. This protocol follows the CONSORT guidelines [34].

Psychosocial outcomes include: perceived risk for ipsilateral and contralateral breast cancer and for ovarian cancer, cancer-related worry and distress; knowledge of genetic aspects of breast cancer; decisional satisfaction; and HRQL. The study also is evaluating women's experience of and satisfaction with RGCT (i.e., the timing and quality of the services provided, the perceived impact on treatment decisions, the perceived need for additional psychosocial support, etc.), and the surgeons' experience with RGCT. Standardized questionnaires are administered at study entry (prior to randomization), and at 6 month and 12 month follow-up (see figure 1). The institutional review boards of all participating hospitals have approved the study. The study is registered at the Netherlands Trial Register (NTR1493) and ClinicalTrials.gov (NCT00783822).

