### Participants

The study sample will be composed of 255 women with a clinically confirmed, newly diagnosed primary breast cancer or ductal carcinoma in situ (DCIS) who meet at least one of the criteria for referral for genetic counseling and DNA analysis according to the Dutch Institute for Healthcare Improvement (CBO). These criteria are: (1) age at time of breast cancer diagnosis less than 35 years; (2) previous history of cancer in the contralateral breast, with the first breast cancer diagnosis at less than 50 years of age; (3) previous personal history of ovarian cancer; (4) a family history of ovarian cancer; (5) a first degree male relative with breast cancer; (6) breast cancer diagnosed under the age of 50 years, with a first degree relative diagnosed with breast cancer under the age of 50 years; (7) breast cancer diagnosed under the age of 50 years, with a relative with prostate cancer diagnosed under the age of 60 years; (8) breast cancer, with two or more relatives from the same side of the family diagnosed with breast cancer, where at least one family member (either the patient or a relative) was diagnosed under the age of 50 years; or (9) a proven *BRCA1/2 *mutation in the family. Women who meet one or more of these criteria are considered to have a 10% or greater chance of having a BRCA1/2 gene mutation [35,36]. Women are excluded from the study if they are younger than 18 years of age, lack basic fluency in the Dutch language, are incapable of understanding informed consent, or are diagnosed with a breast cancer recurrence or with metastastic disease. The patients are being recruited from 12 hospitals in the Amsterdam and Utrecht regions of the Netherlands.

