#### Choice of surgical procedure

The patients' definitive surgical treatment decision is determined via medical record audit. Via questionnaires women are asked to report the factors motivating their choice of treatment.

*Risk perception *is assessed with 4 items adapted from previous studies [40-42] that inquire about current perceived risk of recurrent or contralateral breast cancer (all questionnaires), of ovarian cancer, and of the possibility of having hereditary breast cancer (follow-up questionnaires). Women are asked to rate on a 5-point scale how likely they think it is that they will develop cancer again, and to rate their perceived risk on a continuous scale from 0% to 100%.

*Cancer worries *are assessed with 8 items, 6 of which are adapted from previous work by Watson [40,43], that measure the frequency of cancer-related worries, their impact on mood, and their impact on daily functioning.

The Hospital Anxiety and Depression Scale (HADS) [44] is used to assess *psychological distress. *The HADS contains 14 items. Both a total score and separate scores for anxiety and depression can be calculated. The HADS has been validated for use in the Dutch population, showing good psychometric properties, with Cronbach's alphas for both the anxiety and depression scales >0.70 [45-47].

*Cancer-specific distress *is assessed with the Impact of Events Scale (IES), a 15-item Likert-scale organized into 2 subscales: intrusive thoughts and feelings, and avoidance of thoughts and feelings related to the stressful situation. In this case, the stressful situation is the diagnosis of breast cancer [48]. The IES has high levels of internal consistency (alpha's above 0.80) and has been translated and validated for use in the Dutch setting [49].

*Satisfaction with decision-making *is assessed with the Satisfaction with Decision Scale (SWD) [50] and the Decisional Conflict Scale [51,52]. The 6-item SWD-scale can be adapted to any medical decision and, in this case, refers to the choice of surgical treatment. The scale has high internal consistency reliability (alpha = 0.86) [50]. The 16-item Decisional Conflict Scale contains three subscales: 'Uncertainty', 'Factors contributing' and 'Effective decision making'. The scale had high internal consistency reliability (alpha of the three subscales ranges from 0.75-0.82 in the Dutch version).

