### Sample size

The sample size calculations are based primarily on the type of surgery chosen, and specifically on the uptake of bilateral mastectomy. With a total sample of 255 women (170 in the RGCT arm and 85 in the UC arm), the study will have 80% power to detect a difference of 18% versus 5% in the uptake of bilateral mastectomy, with the p-value set at 0.05. The sample size ratio of 2:1 was chosen to ensure that the RGCT sample is sufficiently large to obtain stable estimates of bilateral mastectomy and delayed prophylactic contralateral mastectomy uptake among *BRCA1/2 *carriers, and to allow for secondary analyses (e.g., to examine predictors of DNA testing uptake). The percentages indicated above are based on the following assumptions: (1) based on the participating hospitals' experiences in the previous three years, 5% of the women in the UC arm are expected to choose bilateral mastectomy; (2) in the RGCT arm, it is expected that 20% will test positive for a *BRCA1 *or *BRCA2 *mutation, of whom, on average, 50% will opt for a bilateral mastectomy. Of the remaining 80% of women in the RGCT arm, we expect a 10% uptake of bilateral mastectomy. For the remaining, primarily self-report outcomes (e.g., cancer worries and cancer-specific distress, decisional satisfaction, HRQL), the sample of 255 participants is more than sufficient to detect a 0.5 standard deviation between-group difference in mean scores. Based on data obtained from the cancer registries of the Integral Cancer Centers of Amsterdam and Middle Netherlands, and on data provided by the participating hospitals, it is estimated that there will be a total of 2550 newly diagnosed breast cancer patients during the recruitment period. Approximately 15% of these women is expected to be eligible for participation. Based on prior experience with recruitment of patients into similar studies, we expect an 80% response rate. This results in an expected N of 306 patients. This allows for an attrition rate of 17%, while retaining 255 women for the primary analysis.

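### The primary outcome counts direct bilateral mastectomy for any indication but delayed contralateral mastectomy only if prophylactic, so surgery for cancer in both breasts would count as uptake and dilute the comparison

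*Protocol article*

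**What the plan says.** The abstract defines the outcome: "The primary behavioral outcome is the uptake of direct bilateral mastectomy or delayed prophylactic contralateral mastectomy". The opening of Methods/Design repeats it as "the uptake of direct BLM or of delayed CPM", where CPM is the article's abbreviation for the prophylactic contralateral operation. Hypotheses 1 and 2 under Objectives and research hypotheses keep the split. The first names direct bilateral mastectomy (BLM) with no indication, and the second names a delayed contralateral mastectomy that is prophylactic.

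Under Participants, women are excluded for age under 18, language, capacity to consent, "or are diagnosed with a breast cancer recurrence or with metastastic disease". Cancer or DCIS in both breasts at diagnosis is not listed. Criterion 2 enrols women with an earlier cancer in the other breast.

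Under Choice of surgical procedure, "The patients' definitive surgical treatment decision is determined via medical record audit". Nothing in the article classifies the surgery on each side as treatment or prevention.

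The Background gives the rationale: "BLM and delayed contralateral prophylactic mastectomy (CPM) substantially reduce the risk of contralateral breast cancer". The Sample size section assumes that "5% of the women in the UC arm are expected to choose bilateral mastectomy", from the hospitals' previous three years, and does not split that figure by indication.

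**The concern.** The intended construct is a woman's decision to have a breast removed that does not currently need cancer surgery. Three records, scored by the printed definition:

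- **(a)** Cancer in one breast, and the other, healthy breast removed at first surgery: event, as intended.
- **(b)** Cancer in both breasts at diagnosis, both removed at first surgery: event, although both sides were treated for cancer.
- **(c)** Cancer in one breast, a second cancer found in the other after first surgery, and that breast then removed: no event, because the second operation was not prophylactic.

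Records (b) and (c) are both treatment of cancer on both sides, yet they score oppositely. If (b) occurs, it adds to both arms events that depend less on the offer of rapid testing than those in (a). That raises the usual care (UC) rate and lowers the ratio and the power. It also clouds two secondary aims. One is stable estimates of uptake among carriers, of whom about 34 are expected in the RGCT arm (20% of 170). The other is the analysis of factors associated with BLM, where bilateral disease would be an obvious but uninformative predictor.

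**Working it through.** **Inputs from the Sample size section.** 170 RGCT and 85 UC; 18% versus 5%; alpha 0.05, taken as two-sided; power 80%. The 18% follows from the stated assumptions: 0.20 × 0.50 + 0.80 × 0.10 = 0.18.

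**The plan's own figure.** Continuity-corrected power = Φ[(d − c − 1.96·SE0)/SE1], where d is the difference, c = ½(1/85 + 1/170) = 0.0088, SE0 is the pooled and SE1 the unpooled standard error. At 5% and 18%, SE0 = 0.0456 and SE1 = 0.0378, so Φ[(0.130 − 0.0088 − 0.0894)/0.0378] = Φ(0.84) = 80.0%. The stated power is reproduced and the sample size is not in error. Exact enumeration of the uncorrected chi-square gives 87.4%.

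**Why a few cases count.** Expected events are 85 × 0.05 = 4.25 in UC and 170 × 0.18 = 30.6 in RGCT. One extra woman in UC adds 1/85 = 1.2 points to a 5% rate.

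**Assumptions, not in the documents.** b = share of entrants with cancer in both breasts, 1–3%; q = share of those who have both breasts removed, 50–100%.

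**Case A: these women come on top of the planned rates.** UC rate = bq + (1 − b) × 0.05; RGCT rate = bq + (1 − b) × 0.18; difference = (1 − b) × 0.13.

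At b = 2% and q = 75%, bq = 0.015. UC = 0.015 + 0.049 = 6.4% and RGCT = 0.015 + 0.1764 = 19.1%. The treatment-only share of UC events is 0.015/0.064 = 23%. Corrected power is Φ[(0.1274 − 0.0088 − 1.96 × 0.0473)/0.0402] = 74.0%.

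| b | q | UC | RGCT | Difference (points) | Ratio | Power, corrected | Power, exact uncorrected |
|---|---|---|---|---|---|---|---|
| 0 | – | 5.0% | 18.0% | 13.0 | 3.6 | 80.0% | 87.4% |
| 1% | 50% | 5.5% | 18.3% | 12.9 | 3.4 | 77.8% | 85.5% |
| 2% | 75% | 6.4% | 19.1% | 12.7 | 3.0 | 74.0% | 82.1% |
| 3% | 75% | 7.1% | 19.7% | 12.6 | 2.8 | 71.1% | 79.3% |
| 3% | 100% | 7.9% | 20.5% | 12.6 | 2.6 | 69.1% | 77.2% |

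If these women are set aside instead, leaving 98% of each arm at b = 2%, the rates return to 18% versus 5% and corrected power is 78.9%.

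**Case B: they are already inside the planned rates.** The stated power then stands. Setting them aside gives UC = (0.05 − bq)/(1 − b) and RGCT = (0.18 − bq)/(1 − b). At q = 100%, b = 1% gives 4.0% versus 17.2% with 83.4% corrected power, and b = 3% gives 2.1% versus 15.5% with 90.5%.

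**The case against.** The best reply is that the article treats BLM throughout as an elective, risk-reducing step. The abstract lists it as preventive surgery, the Background presents it as an alternative to unilateral mastectomy, and the outcome is phrased as uptake. A reader would know what is meant, and coding each breast could sit in an audit form that is not shown. This establishes intent, but it is not a scoring rule. The printed outcome attaches an indication to one half only, and does so consistently, and no listed exclusion closes the gap.

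Several other replies stand:

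- The frequencies are assumed; the article never mentions bilateral cancer at diagnosis.
- The 5% is drawn from hospital experience with bilateral mastectomy, with no qualifier, so it may well include treatment-only cases. No stated power is then lost.
- The Statistical analyses section names the chi-square test without mentioning a correction. Uncorrected, power stays above 80% in the 2% and 75% scenario.

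A reader might infer that the operations at issue are wholly unaffected by testing. The article does not support that: a woman with cancer in both breasts might choose mastectomy over conservation on a DNA result.

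A reader might also infer bias from timing, because waiting 3 to 6 weeks for a result gives a second cancer more time to appear before surgery. On the article's 3% annual contralateral risk in carriers, six weeks among 34 carriers gives 34 × 0.03 × 6/52 = 0.12 women. Applying that rate to all 170 gives only 0.59. This argument should not be pressed.

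**Conclusion.** The point holds as a flaw in the outcome definition. As printed, bilateral mastectomy performed to treat cancer in both breasts counts as uptake in either arm, while the equivalent delayed operation does not. Randomisation balances such women in expectation, so it would be wrong to infer a biased comparison or an inflated type I error. The consequences are dilution and an uptake rate that does not measure what it is meant to measure.

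The size cannot be fixed from the documents. With 1–3% bilateral disease and 50–100% of those women having both breasts removed, on top of the planned rates, the absolute difference moves by at most 0.4 points. The ratio falls from 3.6 to between 3.4 and 2.6, and corrected power falls from 80% to between 78% and 69%. If the planned rates already include these cases, the stated power is correct and a consistent definition would improve it. In both cases a consistent definition gives more power than the printed one. It is worth correcting, but it does not undermine the trial.

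**What to change.** 1. **One indication rule for both halves.** Count as an event the removal, at first surgery or later in follow-up, of a breast with no current diagnosis of cancer or DCIS. An earlier, treated contralateral cancer should not disqualify the event. Otherwise women enrolled under criterion 2 whose earlier cancer was treated with breast conservation would be misscored.
2. **Bilateral disease known before randomisation.** Identify it from the diagnosis data, set these women aside from the primary comparison in both arms, and report their surgery separately. Because the characteristic precedes randomisation, this is compatible with the intention-to-treat principle under Statistical analyses.
3. **Sensitivity analysis.** Keep bilateral mastectomy for any indication in all randomised women. This also covers second cancers detected after randomisation.
4. **Sample size section.** State whether the 5% and the 18% include bilateral mastectomy for cancer in both breasts.

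The cost is a few words in the outcome definition and one field on the chart-audit form; diagnosis, tumour characteristics and surgical treatment are already collected. The downside is that a few women leave the primary comparison. In the 2% scenario this takes corrected power to 78.9%, against 74.0% if they are kept and counted as uptake.

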**Discussion:**

This trial will provide essential information on the impact of RGCT on the choice of primary surgical treatment among women with breast cancer with an increased risk of hereditary cancer. This study will also provide data on the psychosocial consequences of RGCT and of risk-reducing behavior.

**Trial registration:**

The study is registered at the Netherlands Trial Register (NTR1493) and ClinicalTrials.gov (NCT00783822).

## Background

### Breast cancer and genetics

Breast cancer is the most frequently occurring malignancy in women in the Netherlands. Approximately 1 in 8 women will develop the disease during their lifetime, resulting in approximately 12,000 new cases annually. A positive family history of breast cancer is the single strongest risk factor for developing the disease. In 5%-10% of the cases, breast cancer has a hereditary basis. In 15%-30% of patients from high-risk families, breast cancer is caused by a germline mutation in the *BRCA1 *or *BRCA2 *gene [1-4]. A similar percentage of breast cancers is expected to have a genetic basis due to mutations in (combinations of) other low penetrance breast cancer susceptibility genes [5]. Current estimates indicate that women who carry mutations in the *BRCA1 *or *BRCA2 *genes have up to an 85% lifetime risk of developing breast cancer, and can also have up to a 60% lifetime risk of developing ovarian cancer [6,7]. Breast cancer patients who carry a *BRCA1/2 *mutation have a 3% annual risk of developing contralateral breast cancer, with the overall risk being as high as 52% by the age of 70 [7,8]. For *BRCA1/2 *carriers who were diagnosed with breast cancer before the age of 40 years, the cumulative risk of developing contralateral breast cancer after a follow up of 25 years is even higher, i.e. 63% [9]. Given these high rates of new primary cancers, breast cancer patients with strong family histories of the disease may benefit from genetic counseling and testing as a means of making a well-informed decision on preventive measures.

### Genetic counseling and testing in breast cancer patients

The objectives of cancer genetic counseling, in general, are to improve knowledge and understanding of the possible genetic basis of the disease, of personal risks of developing cancer, and of the possible consequences of undergoing genetic testing [10,11]. In the case of breast cancer, the goal of genetic counseling is to ensure that women have been sufficiently educated regarding inherited breast/ovarian cancer to make informed decisions concerning genetic testing, and available preventive and treatment options [12,13]. The majority of published studies have found that genetic counseling is effective in increasing knowledge and awareness of cancer risk, and of the consequences of genetic testing [11,14-16]. Factors that may be indicative of hereditary breast cancer are young age at diagnosis, multiple family members with breast cancer, male relatives with breast cancer, breast and ovarian cancer in the family and/or breast cancer and prostate cancer in family members at a relatively young age. Women with one or more of these factors are considered to have a 10% risk or greater of carrying a *BRCA1 *or *BRCA2 *gene mutation, and are thus, in general, considered as candidates for DNA testing. Genetic counseling and DNA testing for breast cancer usually takes approximately 4-6 months to complete. However, some hospitals and non-commercial laboratories are now able to generate test results within 3 to 6 weeks. This technology of *rapid *genetic testing creates new opportunities for providing both women and their treating surgeons with information potentially relevant for deciding between available treatment options, including type of surgery and adjuvant therapy [17-19].

Newly diagnosed patients who learn that they are gene mutation carriers may decide to undergo a mastectomy rather than a lumpectomy, or bilateral mastectomy (BLM) rather than unilateral mastectomy. Recent studies have shown that BLM and delayed contralateral prophylactic mastectomy (CPM) substantially reduce the risk of contralateral breast cancer, while studies on survival have yielded mixed results [20-23]. Additionally, women who choose unilateral or bilateral mastectomy as their initial surgical treatment will often be spared the necessity of undergoing radiation therapy. However, rapid genetic counseling and testing (RGCT) may necessitate some delay in surgical treatment until DNA test results are available. Previous studies have indicated that the majority of newly diagnosed breast cancer patients at high risk of being *BRCA1/2 *mutation carriers will accept the invitation to undergo RGCT, and that the DNA test results can have a substantial impact on the choice of surgery [3,24,25]. In these British and American studies, between one-half and two-thirds of the breast cancer patients carrying a *BRCA1 *or *BRCA2 *mutation opted for a bilateral mastectomy, with some opting for a delayed CPM instead of direct BLM. Additionally, between 16% and 24% of high-risk patients who test negative for a *BRCA1/2 *mutation opted for BLM [3,25].

The psychosocial impact of genetic testing in recently diagnosed breast cancer patients has been the subject of only limited study [26]. Although disclosure of test results may increase short term psychological distress, there is no evidence to suggest that there is a sustained increase in levels of distress as a result of such counseling or testing [26-28]. A Dutch study showed that an active approach to genetic counseling in patients recently diagnosed with breast cancer and in an early stage of primary treatment (i.e. 7-8 weeks after surgery), did not increase psychological stress significantly [27,28]. In addition, in a small pilot study in 8 women who were offered RGCT following their breast cancer diagnosis but prior to surgery, none reported that the offer of RGCT had added significantly to the stress that they were already experiencing due to the diagnosis of breast cancer [29]. There is also relatively little known about the psychological impact of BLM or CPM. The few studies performed, to date, all but one of which was retrospective in nature, have reported high levels of satisfaction with CPM and no adverse effects on health-related quality of life (HRQL) [30-32].

To summarize, recent advances in the technology of genetic testing for breast cancer open the possibility of offering women with a suspected hereditary form of the disease the opportunity to undergo RGCT in the period of time between receiving the diagnosis and undergoing primary treatment. For those high-risk women who opt for direct BLM or delayed CPM, there are clear advantages in terms of reduction in the risk of contralateral disease, although an improvement in survival has not yet been convincingly demonstrated [20,22]. Women who choose for (bilateral) mastectomy can also avoid having to undergo radiotherapy. This, in turn, can improve the results of breast reconstruction [33]. However, there are insufficient data available on the impact of RGCT, when offered routinely to high-risk women, on medical decision-making, and there is relatively little known about the impact of RGCT on cancer-specific distress, treatment satisfaction, and HRQL.

